## Abstract

**Background:**

Guideline-based medical care has been identified to improve outcomes in stroke. However, data acquisition and medical quality management during hospital stay still need to be improved in China. We have developed a computer-based medical data collecting system, together with automated calculation of key performance indicators (KPIs) and regular individualized education, and thus aim to explore whether it can improve the medical care quality of acute ischemic stroke (AIS) during hospital stay in stroke centers.

**Methods:**

The individualized quality improvement based on the Computer Analysing system to improve Stroke management quality Evaluation (CASE) trial is a prospective, multicenter, historical control study among 30 stroke centers in China. In this trial, the data is directly extracted from the saved original medical record of each AIS patient during hospital stay, regardless of different Electronic Medical Record System (EMRS) in each center. Then, the automated calculation of KPIs and the regular education via teleconference per month allow the clinicians to examine the causes of non-compliance of guideline-based care and develop programs to decrease their frequency.

**Discussion:**

We compare KPIs between pre-intervention stage and post-intervention stage (without or with education) among stroke centers. If proved effective, this approach might be generalized around China and even worldwide, where a unified EMRS is difficult to be applied and in-patient care needs to be improved.

**Trial registration:**

ClinicalTrials.gov NCT03684629. Registered on 9 December 2018. Retrospectively registered.

## Background

Stroke burden has increased over the past three decades in China, emerging to be the leading cause of mortality [1, 2]. A systematic review indicated that implementing clinical guidelines improved the quality and efficiency of medical care [3]. Moreover, studies such as GOLDEN BRIDGE [4], The Get With The Guidelines (GWTG) [5], and BRIDGE STROKE [6] also indicated that increased delivery of in-patient care based on guidelines could contribute to the favorable outcome of stroke patients [7].

To enhance the medical care quality by increasing the compliance with evidence-based performance in stroke patients, China Stroke Center Alliance (CSCA) has been launched in China in 2015. CSCA prompted 13 key performance indicators (KPIs) of acute ischemic stroke (AIS) to monitor the routine in-patient medical care quality, based on the AIS guidelines, involving intravenous thrombosis (IVT), antiplatelet therapy, anticoagulant therapy, and so on [8–13]. Then afterwards, CSCA annually collected the required data from about 20,000 in-patients among more than 1500 stroke centers [14], and calculated and feedback all of the KPIs to each center.

However, there is a huge diversity in the Electronic Medical Record System (EMRS) in different stroke centers in China currently, which makes it difficult to capture all KPIs from the original medical records by a unified system in each center. Accordingly, clinicians in each stroke center have to report the medical data online manually to achieve the feedback of KPIs from CSCA. Indeed, this is also the way data was collected in the above studies (GOLDEN BRIDGE, GWTG, BRIDGE STROKE).

Obviously, this kind of collection has its inherent shortcomings, including the vast cost of manpower and time from clinicians, and questioning of its authenticity due to the lack of traceability of original medical records and enough quality control of data. To minimize the above limitations, we thus developed a computer-based medical data collecting system, with subsequent automated calculation of KPIs and regular individualized education to improve the adherence to guideline-based care. The main purpose is to decrease the workload of clinicians in stroke centers on reporting data manually. We designed this individualized quality improvement based on the Computer Analysing system to improve Stroke management quality Evaluation (CASE) trial to explore whether this novel approach can improve inpatient medical care quality of AIS in each stroke center.

## Method and design

### Design

This is an 18-month prospective, multicenter, historical control study among 30 stroke centers in Zhejiang Province, China. Stroke centers with in-hospital stroke patients voluntarily participate in this trial. All medical documents of consecutive AIS patients admitted in the stroke center according to ICD-10 (I63 and G45) are collected by investigators from Zhejiang Stroke Quality Control Center (ZSQCC). Only the de-identified documents are preserved in a safe information database. The clinical data involved in this study belong to the scope of information collection of routine clinical practice. The local infrastructure and characteristics of each recruited center are also recorded. The study protocol is approved by the Institutional Review Board of the Second Affiliated Hospital of Zhejiang University (SAHZU). Because patient information in the CASE is de-identified and anonymized before being released to the researchers, the informed consent requirement is waived by SAHZU Institutional Review Board. All the protocol item is standardized (see Additional file 1). It was registered at ClinicalTrials.gov (NCT03684629).

There are two stages in this trial: pre-intervention stage (the initial 6 months) and post-intervention stage (the next 12 months). We collect the consecutive data of each center during the pre-intervention stage without feedback of KPIs and then monthly send its own KPIs to each center during the post-intervention stage. We finally compare the changes of KPIs from pre-intervention stage to the last 6 months of post-intervention stage (Fig. 1).

**Fig. 1 Fig1:**
[figure not shown]
Flow diagram of the process throughout the trial

### The inclusion criteria for the analysis of medical documents

Patients 18 years or olderAIS confirmed by computed tomography (CT) or diffusion-weighted imaging (DWI)Admitted within 7 days from symptom onset

### Data monitoring and confidentiality

After discharge, the original medical document of each patient during hospital stay is saved as images or portable document format (PDF). Specific software recognizes and pre-processes the above material and sends it to multiple Optical Character Recognition (OCR) [15] engines to build documents with recognized text, which are subsequently re-segmented and synthesized in the post-processing. Required data is extracted from the processed text. Three hundred medical documents were randomly selected to evaluate the error rate of the extraction, i.e., the rate of inconsistent data extracted by computer-based medical data collecting system and manual input of neurologists, which was finally 3.4%. Previous report has also demonstrated generalizability and applicability of OCR with a positive predictive value of 94.6% [16]. This software also allows the trained study investigators to quickly check the quality of extracted data by pointing out the original extraction site, enabling the authenticity and traceability of original data. The checked data are then imported into the analyzing system, and KPIs will be calculated according to the designed formula (Fig. 2).

**Fig. 2 Fig2:**
[figure not shown]
The procedure to improve the quality of the medical care in stroke patients

### Intervention for medical care improvement

Individualized quality improvement process is divided into 3 steps:
Each stroke center receives their own KPIs monthly, as well as the average KPI level of all 30 stroke centers as contrast, which are automatically calculated by computer analyzing system.Based on the performance of KPI data, stroke experts from ZSQCC identify the items which need to be improved, provide each center with relevant education of guidelines, and help the clinicians to examine the causes of non-compliance of guideline-based care and develop programs to decrease their frequency via regular teleconference per month and face-to-face lectures quarterly. In the meantime, stroke centers with the best KPI performance also share their experiences on medical care improvement.Each stroke center is then required to provide a detailed improvement plan for each KPI and check whether it is implemented one by one during the next teleconference.

### Outcome

The primary outcomes are as follows: 7 KPIs including the accomplishment of National Institutes of Health Stroke Scale (NIHSS), intravenous thrombosis within 4.5 h of onset, antiplatelet agent therapy within the first 48 h, statin use after hospitalization and at discharge, antithrombotic therapy at discharge, and anticoagulant treatment for patients with atrial fibrillation at discharge [8, 9, 11–13] (see Additional file 2).

The secondary outcomes are as follows: 9 KPIs including prevention of deep vein thrombosis, blood vessel evaluation within 1 week of hospitalization, swallowing function evaluation, blood lipid level assessment, rehabilitation evaluation and implementation, recommendation of life style change, anti-hypertensive therapy, hypoglycemic treatment at discharge, and recurrence rate [10, 11, 17] (see Additional file 2).

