### Sample size

Among all the KPI, the adherence to intravenous thrombosis (IVT) was poor in china [18]. Result of investigation in Zhejiang before the trial indicated that only approximately 8% of ischemic stroke patients received IVT 4.5 h after stroke onset. To detect 10% improvement in the adherence to IVT, with *α* = 0.05 and power = 90%, at least 16,570 patients will be needed in pre-intervention stage and post-intervention stage.

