## Conclusion

In summary, this is a new mode to improve in-patient medical care, which consists of advanced acquisition technique and personalized feedback with persistent education. It can yield real benefits in terms of increased delivery of guideline-based care and reduced manual reporting of clinicians. If proved effective in Zhejiang province, this new quality improvement approach might be generalized around China and even worldwide, where a unified EMRS is difficult to be applied.

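### Seven KPIs are primary with no success rule, but only IVT is sized, so neither the error rate nor the power of the primary claim is fixed

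*Protocol article*

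**What the plan says.** - **Outcome section.** "The primary outcomes are as follows: 7 KPIs including the accomplishment of National Institutes of Health Stroke Scale". The other six are IVT, early antiplatelet therapy, statin use in hospital, statin use at discharge, antithrombotic therapy at discharge, and anticoagulation at discharge in atrial fibrillation. All seven carry the same label. None is ranked first and no composite is defined.
- **Sample size section.** Only IVT is sized. The reason given is "Among all the KPI, the adherence to intravenous thrombosis (IVT) was poor in china", and the aim is "To detect 10% improvement in the adherence to IVT". This is the only place where a significance level or a power appears (0.05 and 90%).
- **Planned data statistical analysis section.** The hospital-level rates of all KPIs in the two stages are compared by paired t test. An ITS analysis is also performed. Neither is named as the confirmatory analysis, and no significance level is given for the KPI tests.
- **Conclusion.** "If proved effective in Zhejiang province, this new quality improvement approach might be generalized". What would count as proof is not defined there or elsewhere in the article.

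**The concern.** The choice of primary outcomes and the outcome that is powered are both fixed in this document, and they do not match: seven are primary and one is sized. Which result would establish that the approach works is left open, and each reading has a cost.

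If any one KPI were enough, improvement in an easily documented item such as NIHSS completion would support the same conclusion as improvement in IVT, and the false-positive risk of the overall claim would exceed the nominal level. If all seven were needed, the false-positive risk would be controlled, but the 90% power would describe only one of seven conditions. A reader of the results could not tell which claim the trial was designed to test, although the article links that claim to use of the approach well beyond Zhejiang.

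**Working it through.** **Inputs from the article.** Seven primary KPIs (Outcome). Alpha 0.05, power 90%, IVT baseline about 8%, 10% improvement, at least 16,570 patients (Sample size). Thirty hospitals, paired t test (Planned data statistical analysis).

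**Assumptions, because the article is silent.** Tests are two-sided, each KPI is tested at 0.05, there is no true effect on any of the seven, and correlations between KPI results are equal, ranging from 0 to 0.9.

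**Step 1. The article's own figure.** The article says that "at least 16,570 patients will be needed in pre-intervention stage and post-intervention stage". With equal stages, two-sided 0.05 and 90% power, a relative rise from 8% to 8.8% needs 25,264 per stage, and an absolute rise from 8% to 18% needs 236 per stage. Neither gives 16,570. The closest match is 8% to 9%: 16,343 per stage, or 16,542 with continuity correction. That mismatch is a separate matter. What counts here is that the whole calculation concerns IVT and uses the full 0.05.

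**Step 2. If any one KPI counted.**
- Any significant result, independent tests: 1 − 0.95^7 = 0.302.
- False improvement only (upper 2.5% tail of each test), independent tests: 1 − 0.975^7 = 0.162.

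Simulation with equally correlated normal test statistics, 200,000 draws:

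| Correlation | Any significant result | False improvement |
|---|---|---|
| 0 | 30.1% | 16.2% |
| 0.3 | 27.1% | 13.8% |
| 0.5 | 22.8% | 11.4% |
| 0.7 | 17.6% | 8.8% |
| 0.9 | 11.3% | 5.6% |

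Simulated paired t tests on 30 hospitals (40,000 draws) agree: 30.4%, 27.2%, 23.1% and 15.2% for any significant result at correlations 0, 0.3, 0.5 and 0.8.

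The nominal rate is 5% for the middle column and 2.5% for the right-hand one. False improvement is therefore inflated by 16.2/2.5, about 6.5-fold, at correlation 0. At 0.5 the factor is 11.4/2.5, about 4.6, and at 0.9 it is 5.6/2.5, about 2.2.

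**Step 3. If all seven were required.** The chance that all seven are falsely significant cannot exceed that of any single one, so it is at most 5%. For the same reason, power cannot exceed that of the weakest KPI. As an illustration, if each of the seven had 90% power and the tests were independent, joint power would be 0.9^7 = 0.478.

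**Step 4. Equal primaries with an alpha split.** The strictest Holm step is 0.05/7 = 0.00714. A test sized for 90% power at two-sided 0.05 has an expected standardised effect of 1.960 + 1.282 = 3.242. The critical value at 0.00714 is 2.690, so power is Φ(3.242 − 2.690) = Φ(0.552), about 0.71. To keep 90% at that level, the 8% to 8.8% comparison would need 37,927 per stage instead of 25,264, a factor of 1.50.

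**The case against.** **No passage says one KPI suffices.** A reader might infer that the trial can be declared effective on any one of seven tests, with a false-claim risk of about 30%. The article does not support that as stated. The phrase about proof of effectiveness occurs in prose about generalising the approach, not in a decision rule, and an all-seven reading or KPI-by-KPI reporting is equally open. The 30% also needs independent tests, no effect on any KPI, and results in either direction being counted. Independence is unlikely: the KPIs come from the same 30 hospitals, and several overlap (statin use twice; antiplatelet, antithrombotic and anticoagulant measures). For a false improvement under two-sided tests the ceiling is about 16%; it would be 30% only if 0.05 were one-sided. All of this stands, and it limits the size of the point.

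**Alpha 0.05 is given for sizing, not for each KPI test.** This is correct, so its use for all seven is an assumption. No other level appears in the article.

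**Two analyses per KPI might be counted as 14 tests.** That would overstate the problem. The paired t test and the ITS for one KPI use overlapping data on the same outcome, so they are not separate independent chances of error. The fair criticism is only that neither is given priority.

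**A multiplicity procedure may sit in an analysis plan that is not shown.** This is true, and its absence alone would be no finding. But the list of primaries and the outcome that is powered are fixed here. An equal alpha split added later would take away part of the power that the Sample size section claims for IVT.

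**The intervention addresses every KPI.** Each center must write an improvement plan for each, so putting IVT first is not the only reasonable choice. It is the one that matches the sample size as written.

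**Conclusion.** The concern holds as a mismatch within the protocol: seven equal primaries, one of them sized, and no rule for success. Whichever reading is taken, one operating characteristic is not as stated.

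- **Any one KPI counts:** the chance of some false significant result is up to about 30% (about 23% at correlation 0.5), and of a false improvement up to about 16% (about 11% at 0.5). These figures rest on two-sided 0.05 tests and no true effect on any KPI. The correlations are assumed, since the article gives none.
- **All seven required:** error is at most 5%, but the 90% quoted for IVT is only a ceiling on the power of the claim.

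Confidence is high that the rule is missing and the sizing does not match. The probabilities are conditional illustrations, not the trial's error rate.

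**What to change.** State the success rule in the Outcome and Planned data statistical analysis sections:

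1. Test IVT, the KPI that the sample size is built on, first at 0.05.
2. Name either the paired t test or the ITS as the confirmatory analysis and label the other supportive.
3. Only if IVT succeeds, test the other six KPIs under Holm at overall 0.05, starting at 0.05/6 = 0.0083.

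This leaves IVT at the alpha used for sizing. The cost is that some of the other six may lose nominal significance, and none can be claimed as confirmatory if IVT fails. According to the Trial status section, recruitment began in August 2018, so the change should be dated, explained, and made before the stage comparison is seen.

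If all seven must remain equal primaries, use Holm across the seven and restate the IVT power. It could fall from a nominal 90% to about 71% at the strictest step (0.05/7), and keeping 90% there would take about 1.5 times the patients. If an all-seven rule is what is meant, no alpha split is needed, but the power of the joint claim should replace the IVT figure.

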### Sample size

Among all the KPI, the adherence to intravenous thrombosis (IVT) was poor in china [18]. Result of investigation in Zhejiang before the trial indicated that only approximately 8% of ischemic stroke patients received IVT 4.5 h after stroke onset. To detect 10% improvement in the adherence to IVT, with *α* = 0.05 and power = 90%, at least 16,570 patients will be needed in pre-intervention stage and post-intervention stage.

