### Planned data statistical analysis

Statistical analysis will be performed with SPSS 22.0 (SPSS, Inc., Chicago, USA). Baseline characteristics of each stroke center (see Additional file 3) and the patients enrolled will be analyzed. The achieved rates of all KPIs of 30 hospitals during pre-intervention stage and the last 6 months of post-intervention stage are compared by the paired *t* test. KPIs are also collected at multiple time points before and after intervention. Interrupted time series (ITS) analysis is performed to assess the efficiency on outcome 1 year after the intervention is carried out [19, 20]. The multiple time points before the intervention allow the underlying trend to be estimated, and the multiple time points after the intervention allow the intervention effect to be estimated accounting for the underlying trend. No additional adjusted analyses will be performed. All the information to calculate the KPIs was included in the medical records. The missing data not extracted by a computer will be extracted manually by a clinician. There are no anticipated problems that are detrimental to the participant so that there are no formal stopping rules for the trial. The schedule of enrolment, interventions, and assessments is included in Fig. 3.

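### The sample size of 16,570 does not follow from its stated inputs under either reading of a 10% improvement, and 90% power is not reached if the improvement is relative

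*Protocol article*

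**What the plan says.** All of the sizing stands in the Sample size section of the protocol article. The baseline comes from a survey in the province before the trial: "only approximately 8% of ischemic stroke patients received IVT 4.5 h after stroke onset". The target is given as "To detect 10% improvement in the adherence to IVT", with the error rates "0.05 and power = 90"%. The result is "at least 16,570 patients will be needed in pre-intervention stage and post-intervention stage".

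The section does not say whether the 10% is relative or absolute, whether the test is one- or two-sided, whether 16,570 applies to each stage or to both together, or whether clustering by hospital was allowed for.

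Two other sections bear on how the number is used. Design sets out a "pre-intervention stage (the initial 6 months) and post-intervention stage (the next 12 months" months), and then states the comparison: "We finally compare the changes of KPIs from pre-intervention stage to the last 6 months of post-intervention stage". Planned data statistical analysis says that the rates of the 30 hospitals "during pre-intervention stage and the last 6 months of post-intervention stage are compared by the paired" t test. The comparison is therefore six months against six months, analysed on hospital rates.

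**The concern.** The section prints a baseline, an effect, an alpha, a power and a result, so a reader can check the result against the inputs. They disagree. Missing detail that an article may leave to a fuller document is a separate matter.

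This is the only sample-size justification in the article and the only basis for the 90% power claim. As written, a reader cannot tell whether the trial was sized for a gain of 0.8 points, 10 points or something between. If the relative gain was the target, a non-significant IVT result would be given more weight than the numbers support.

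**Working it through.** **Inputs.** From Sample size: p1 = 0.08, 10% improvement, alpha = 0.05, power = 0.90, stated N = 16,570. From Design: six months against six months, hence 1:1 if admissions are steady (assumption). Sidedness is not stated; two-sided is taken first (z = 1.960 and 1.2816) and one-sided is also shown.

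**Formula, per stage:**
n = [z(α)·√(2p̄(1−p̄)) + z(β)·√(p1(1−p1) + p2(1−p2))]² / (p2 − p1)², with p̄ = (p1 + p2)/2.

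**Attempt to reproduce 16,570**

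*Relative, 8.0% to 8.8%.* p̄ = 0.084.
- √(2 × 0.084 × 0.916) = 0.39229
- √(0.0736 + 0.080256) = 0.39224
- n = (1.960 × 0.39229 + 1.2816 × 0.39224)² / 0.008² = (0.7689 + 0.5027)² / 0.000064 ≈ 25,263

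That is about 50,530 for both stages.

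*Absolute, 8% to 18%.* p̄ = 0.13.
- √(2 × 0.13 × 0.87) = 0.47560
- √(0.0736 + 0.1476) = 0.47032
- n = (0.9322 + 0.6027)² / 0.01 ≈ 235.6, so 236 per stage and 472 in total

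| Reading | Per stage, two-sided | With continuity correction | Per stage, one-sided |
|---|---|---|---|
| 8.0% to 8.8% | 25,263 | 25,512 | 20,590 |
| 8% to 18% | 236 | 255 to 256 | 192 |

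None of these, nor twice any of them, is 16,570. Against the two-sided values, 16,570 is 16,570/25,263 = 66% of the relative per-stage need. It is 16,570/236 = 70 times the absolute per-stage need and 16,570/472 = 35 times the absolute total.

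Other variants do not recover it from the stated inputs either: unpooled and arcsine formulas, a 1:2 allocation, a one-sample test, a Bonferroni correction for seven indicators, and reading the target as 8% to 10% (4,301 per stage). Near matches need inputs that are absent or contradicted:
- 1:3 allocation (16,916 in the smaller stage)
- 85% power with 1:2 allocation (16,262)
- one-sided 80% power with 10% dropout (16,517)

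The approximate nature of the 8% does not help. For a relative 10% gain to need 16,570 per stage, the baseline would have to be about 11.7% two-sided or 9.7% one-sided.

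**Power actually given by 16,570**

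Power = Φ{[(p2 − p1)·√n − z(α)·√(2p̄(1−p̄))] / √(p1(1−p1) + p2(1−p2))}.

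For 8.0% to 8.8%, two-sided:
- 16,570 per stage: (0.008 × √16,570 − 0.7689)/0.39224 = (1.0298 − 0.7689)/0.39224 = 0.665, so power 74.7%
- 16,570 in total, 8,285 per period: (0.7282 − 0.7689)/0.39224 = −0.104, so power 45.9%

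The one-sided values are 83.7% and 58.4%. All four are below 90%.

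For 8% to 18%, patient-level power exceeds 99.9% whether 16,570 is per stage or the total.

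**Detectable rise at 90% power, two-sided.** 8% to 8.99% if 16,570 is per stage; 8% to 9.42% if it is the total split equally.

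**The case against.** **The trial may not be short of power at all.** A reader might infer from the mismatch that the 90% power is missing whichever way the 10% is read. The document does not support that. Under the absolute reading 16,570 is far more than the simple formula asks for, and the stated 90% is exceeded at patient level. The shortfall belongs to the relative reading only, and the article never uses the word relative. This objection stands and limits the conclusion.

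**A clustering allowance may have been left out of the condensed text.** This could explain an excess. With 8,285/30 ≈ 276 patients per hospital per period, a simple design effect of 1 + (276 − 1) × ICC reaches 35 at an assumed ICC of about 0.12. That ICC is not in the article, and the calculation ignores the gain from pairing. So an N above the simple formula would not by itself be an error under the absolute reading. Clustering cannot explain an N below the simple requirement, so it does not help the relative reading.

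**The planned analysis is not a two-proportion test.** This is correct. The paired t test uses 30 hospital rates, and its power depends on the spread of within-hospital changes, which is not given. The percentages above therefore test the section's arithmetic and do not estimate the trial's power.

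**Other layouts come closer.** A one-sided test with 16,570 patients before and 33,140 after gives 91.7% power for 8.0% to 8.8%. That layout is not stated, its own requirement would be 15,470 before the intervention, and the stated comparison is six months against six.

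**Two further inferences should be resisted.** One is that the authors sized the trial for 8% to 9%. That needs 16,342 per stage (16,542 with continuity correction), which is close but not equal, and the target appears nowhere. The other is that 16,570 is an 18-month total with a third discarded. That adds an assumption the text does not make. The interrupted time series also uses post-intervention time points, and the figure is a stated minimum with consecutive admissions, so actual numbers may be larger.

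**Conclusion.** The sample-size sentence is wrong as written: 16,570 does not follow from an 8% baseline, a 10% improvement, alpha 0.05 and 90% power under either reading of the improvement, per stage or in total.

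The consequence depends on a point the article leaves open:
- **Relative gain meant:** 90% power is not reached. It is about 75% or 46% two-sided (84% or 58% one-sided), according to whether 16,570 is per stage or the total of the two compared periods.
- **Absolute gain meant:** the number is 35 to 70 times the simple requirement, with no explanation given, and power is not in question at patient level.

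These results assume independent patients and equal periods. They say nothing firm about the power of the paired t test on hospital rates. That the figure does not reproduce rests on the section's own inputs. That the trial is underpowered is not established.

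**What to change.** Restate the sample-size sentence from the assumptions actually used: both target rates (with the scale of the 10% made explicit), sidedness, any clustering allowance with its ICC, and whether 16,570 is per stage or the total for the two compared six-month periods. Then give a power or a detectable difference that reproduces from them.

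The right text depends on what was intended:
- **If 8.0% to 8.8% is kept:** state about 75% power at 16,570 per stage (two-sided, before clustering). Alternatively, state that 16,570 per stage detects a rise of about 1 point from 8% with 90% power, presented as what the number delivers and not as the original target.
- **If 8% to 18% was meant:** say so, and give the reason for the large excess over 236 per stage.

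The change is wording only and needs no extra patients. Its cost is that, under the relative reading, the stated power or detectable effect becomes less favourable.
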